## **Abstract**

**Introduction:** Retrograde intrarenal surgery (RIRS) is a primary treatment modality for urinary tract stones, and successful placement of the ureteral access sheath (UAS) is a critical procedural step. Preliminary studies have suggested that preoperative electroacupuncture (EA) may improve UAS placement success rates, reduce ureteral injury, and enhance stone clearance outcomes. This trial evaluates the efficacy and safety of EA as an adjunctive therapy in first-stage RIRS.

**Methods and analysis:** This multicenter, randomized, single-blind, sham-controlled trial will enroll 120 adult patients with upper ureteral or renal stones ( $\geq 10$  mm) scheduled for first-stage RIRS. Participants were randomly allocated (1:1) to receive either preoperative EA combined with general anesthesia or sham EA combined with general anesthesia across multiple treatment sessions. The primary outcome is the proportion of patients achieving successful UAS placement during first-stage RIRS. Secondary outcomes included operative time, resistance during UAS insertion, ureteral injury (assessed via the Post-Ureteroscopic Lesion Scale [PULS]), stone clearance rate at 2 weeks postoperatively, and adverse events (AEs) within 2 weeks postoperatively. Data will be analyzed using the intention-to-treat principle.

**Discussion:** This study will be the first randomized controlled trial (RCT) to investigate the efficacy of EA in improving both the success rate and safety of UAS placement during first-stage RIRS. The findings will provide high-quality evidence to support the integration of EA as an adjunctive therapy in clinical practice. Through comprehensive multidimensional assessments, this research will demonstrate the potential for broader application of EA in urolithiasis management. Further rigorously designed clinical trials will be essential to validate and refine this promising therapeutic approach.

## **Study Protocol**

### **1. Study background**

1. RIRS will serve as a cornerstone intervention for urinary tract calculi, with the successful placement of the UAS during the procedure being a pivotal step.

Identifying strategies to effectively improve UAS deployment success rates will be critical.

Urolithiasis will remain a prevalent condition in urology, with recent epidemiological surveys projecting a prevalence rate of 1.61%–20.45% in China, an

aggregate rate of 7.54%, and a rising trend [1]. Minimally invasive endoscopic procedures, including rigid ureteroscopy, flexible ureteroscopy, percutaneous nephrolithotomy, and laparoscopic lithotomy, will be required for many patients [2]. Advancements in technology will establish RIRS as a primary modality for urinary stone management. During RIRS, the placement of the UAS will constitute the initial and crucial procedural step [3]. Successful UAS insertion will depend on mitigating resistance caused by ureteral spasm secondary to stone obstruction and inherent ureteral strictures. Excessive force during sheath placement will risk ureteral injury, including perforation, avulsion, or rupture [3]. However, quantitative thresholds defining "excessive force" will remain undefined. While studies will identify risk factors influencing insertion resistance [4–6], effective protocols to reduce resistance and ureteral trauma during first-stage RIRS will not yet be established. Preoperative alpha-blocker therapy administered one week prior to surgery will enhance UAS placement success rates in first-stage RIRS. However, patients presenting with acute pain may find a one-week medication delay incompatible with their urgent need for symptom relief. Thus, developing approaches to expedite surgery while optimizing UAS insertion success will be imperative.

2.EA—demonstrating potential to relax ureteral smooth muscle effectively.

However, whether EA can enhance the success rate of UAS placement during first-stage RIRS will remain unexplored.

Clinically, acupuncture will exhibit efficacy across diverse conditions: alleviating pain (e.g., headaches, musculoskeletal pain, arthritis), treating neurological disorders (e.g., facial paralysis, post-stroke sequelae, insomnia), and modulating gastrointestinal function (e.g., gastralgia, diarrhea, constipation). It will also address gynecological, andrological, and otorhinolaryngological ailments. Compared to modern medicine,

acupuncture will retain unique advantages, including simplicity, cost-effectiveness, and minimal adverse effects, often yielding unexpected benefits for chronic and refractory diseases. Furthermore, its integration with therapies such as electrical stimulation will enhance therapeutic outcomes.

EA, an adjunctive therapy integrating acupuncture with modern medicine, has demonstrated significant clinical efficacy in alleviating various types of muscle spasms and pain [5–6]. Research indicates that EA exerts a multifaceted relaxant effect on ureteral smooth muscle, primarily through the following mechanisms:

## 2.1 Neuromodulatory Mechanisms

2.1.1 Neural Pathway Activation: EA stimulates specific acupoints, activating sensory afferent pathways of the nervous system. These signals are transmitted to the central nervous system (CNS), triggering neural reflexes that modulate autonomic nervous system (ANS) activity. By regulating the balance between sympathetic and parasympathetic activity, EA influences ureteral smooth muscle tone. Parasympathetic excitation induces ureteral smooth muscle relaxation, facilitating urine drainage, whereas sympathetic activation may promote contraction.

2.1.2 Neurotransmitter Release: EA stimulation promotes the release of neurotransmitters such as endorphins and acetylcholine (ACh). Endorphins exert analgesic effects and directly relax smooth muscle, including the ureter. Acetylcholine modulates ureteral contraction and relaxation under certain conditions, suggesting that EA may regulate ureteral function via ACh-mediated pathways.

## 2.2 Endocrine Regulatory Mechanisms

2.2.1 Hormonal Modulation: EA may modulate the endocrine system to influence hormone secretion and release, thereby affecting ureteral smooth muscle function. Key mediators such as prostaglandins and nitric oxide (NO) play critical roles in

ureteral motility regulation. EA may adjust the synthesis and release of these hormones, altering ureteral smooth muscle tone.

2.2.2 Fluid-Electrolyte Balance: The endocrine system also regulates fluid-electrolyte balance, indirectly impacting ureteral function. By modulating renal water and electrolyte excretion, EA may influence urine production and flow, subsequently affecting ureteral pressure and peristalsis.

### 2.3 Local Tissue Regulatory Mechanisms

2.3.1 Enhanced Blood Circulation: EA promotes local blood circulation, improving oxygen and nutrient delivery while reducing the accumulation of metabolic byproducts. This mitigates tissue edema and inflammation, alleviating ureteral smooth muscle spasm.

2.3.2 Muscle Tone Regulation: EA may directly regulate ureteral smooth muscle tone. Stimulation of specific acupoints induces alternating contraction and relaxation of local muscles, modulating ureteral tension through neural reflexes, humoral regulation, or direct mechanical stimulation.

The mechanisms underlying EA-induced ureteral smooth muscle relaxation are multifaceted, involving neuroendocrine and local tissue regulation. While research into these mechanisms remains ongoing, EA—a fusion of traditional and modern therapeutic approaches—has demonstrated clinical efficacy in relieving ureteral spasms and enhancing urinary drainage.

3. Preliminary experiments conducted by our research team have demonstrated that EA significantly enhances the success rate of UAS placement, reduces ureteral injury, and improves stone clearance rates during first-stage RIRS, warranting further investigation.

Preliminary investigations by our research team have demonstrated that EA significantly enhances the success rate of UAS placement, mitigates intraoperative ureteral injury, and improves stone clearance rates during first-stage RIRS. The observed efficacy may be attributed to EA's multifaceted mechanisms. First, optimizing UAS placement is critical to procedural success, as it serves as the foundational step in RIRS. By modulating ureteral smooth muscle tone, EA likely induces relaxation, thereby facilitating sheath insertion, reducing operative time and technical challenges, and enhancing overall procedural safety. Second, EA's ability to minimize ureteral trauma addresses a major intraoperative risk. Ureteral injury during RIRS may lead to postoperative complications such as strictures or urinary leakage. EA appears to exert protective effects by improving local microcirculation and attenuating inflammatory responses, thereby preserving tissue integrity. Finally, improved stone clearance is vital for patient recovery, as residual calculi increase recurrence risks and impose physical and economic burdens. EA may enhance intraoperative stone expulsion by promoting ureteral peristalsis and optimizing urinary drainage.

In-depth exploration of the mechanisms underlying EA in RIRS could yield novel therapeutic strategies for clinical practice. Future studies should prioritize optimizing EA parameters (e.g., stimulation intensity, frequency) and acupoint selection to maximize efficacy and safety. Integrating advanced medical technologies, such as real-time imaging and physiological monitoring, may further elucidate EA's impact on ureteral function, providing a robust scientific foundation for its clinical application.

Given the promising role of EA in first-stage RIRS, dedicated research efforts are warranted to validate its potential in enhancing UAS placement success, reducing

intraoperative ureteral trauma, and improving stone clearance rates. To address this, we propose expanding sample sizes in subsequent trials to strengthen evidence reliability.

This randomized, single-blind, placebo-controlled, multicenter clinical trial will enroll eligible participants to evaluate EA versus sham EA as an adjunct to first-stage RIRS. Key endpoints include UAS placement success rates, procedural safety (e.g., ureteral injury incidence), and stone-free outcomes, with the goal of establishing EA as a standardized adjunctive protocol.

## **2.Study object**

The inclusion criteria for this study are explicitly defined as follows: (1) Voluntary participation in the trial with written informed consent provided and signed by the participant or their legal representative; (2) Age between 18 and 75 years (inclusive); (3) Confirmed diagnosis of upper ureteral or renal calculi (long-axis diameter  $\geq 10$  mm) via urinary tract CT imaging; (4) Scheduled for first-time ureteral stent placement.

Exclusion criteria are delineated in detail: (1) Patients with acute genitourinary infection or febrile conditions; (2) Individuals with a history of alpha-blocker use; (3) Those with solitary kidney, congenital urethral/ureteral malformations, or prior corrective surgeries; (4) Participants exhibiting acupuncture procedure-related phobia; (5) Enrollment in other clinical trials within the preceding three months; (6) Any additional conditions deemed by investigators to compromise trial integrity or participant safety.

### **3.Study design**

This study is a randomized, single-blind, placebo-controlled, parallel-group, multicenter clinical trial with a superiority design, aimed at preliminarily evaluating the efficacy and safety of EA compared to sham EA in improving the success rate of UAS placement during first-stage RIRS. A total of 120 patients with urinary tract calculi requiring first-time ureteral stent placement under general anesthesia will be enrolled and rigorously randomized into the EA group or sham EA group.

Comprehensive clinical data will be prospectively collected and analyzed to establish a robust scientific foundation for optimizing therapeutic strategies in urolithiasis management.

### **4.Sample size estimation**

Based on preliminary trial results demonstrating a 90% success rate of UAS placement in the EA group compared to 75% in the sham EA group, this study adopts a conservative estimate that EA will yield at least a 15% superiority over sham EA for sample size calculation. With a two-sided significance level of 0.05, a 1:1 allocation ratio between groups, and 0.28 confidence interval width, a total of 110 participants (55 in the EA group and 55 in the sham EA group) are required to detect this superiority. Accounting for a potential 10% attrition rate, the adjusted sample size is 120 patients.

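### The 110 patients come from a confidence-interval-width calculation, yet the protocol says they are what detecting superiority requires; power for the assumed effect is about 55%

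*Protocol*

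**What the plan says.** Section 4 of the protocol (Sample size estimation) takes its rates from preliminary results: "90% success rate of UAS placement in the EA group compared to 75% in the sham EA group". It then says that "this study adopts a conservative estimate that EA will yield at least a 15% superiority over sham EA for sample size calculation". The other inputs are a "two-sided significance level of 0.05", 1:1 allocation and a confidence interval width of 0.28. From these it concludes that "a total of 110 participants (55 in the EA group and 55 in the sham EA group) are required to detect this superiority", and it raises the total to 120 for attrition. No power is stated.

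Section 3 (Study design) calls the trial a superiority design, "aimed at preliminarily evaluating the efficacy and safety of EA".

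**The concern.** An interval-width criterion and a detection criterion answer different questions. The first fixes how long the interval for the difference is expected to be. The second fixes how likely that interval is to exclude zero when the assumed effect is real. Section 4 uses the first and reports the second.

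The chosen width makes the gap matter. A full width of 0.28 is a half-width of 0.14, just below the assumed difference of 0.15. The lower limit therefore clears zero only if the observed difference comes out at about the assumed value or higher, which is not far from even odds.

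Anyone reading section 4 to judge whether the trial can answer its question is told that it is sized to detect the effect. If electroacupuncture works exactly as assumed, the comparison would still miss significance about 45% of the time, and slightly more than half the time under Fisher's exact test. Calling the effect conservative adds to the impression of a safety margin that is not there.

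**Working it through.** **Inputs, all from section 4:** p1 = 0.90 (electroacupuncture), p2 = 0.75 (sham), difference 0.15, two-sided alpha 0.05 (z = 1.96), 1:1 allocation, full interval width 0.28.

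**Step 1. Reproduce the protocol's figure.** Wald interval for a difference of two proportions:

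n per arm = (2 × 1.96 / w)² × [p1(1 − p1) + p2(1 − p2)]

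- (3.92 / 0.28)² = 14² = 196
- 0.90 × 0.10 + 0.75 × 0.25 = 0.09 + 0.1875 = 0.2775
- 196 × 0.2775 = 54.4, rounded up to 55 per arm, 110 in total

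This matches exactly. The expected interval at 55 per arm is 0.15 ± 0.139, that is 0.011 to 0.289.

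**Step 2. See whether a conventional power calculation also gives 55.** Pooled normal formula, with mean rate 0.825:

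n per arm = [1.96 √(2 × 0.825 × 0.175) + z_power √0.2775]² / 0.15²

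- 80% power (z = 0.8416): (1.053 + 0.443)² / 0.0225 = 99.5, so 100 per arm
- 90% power: 133 per arm

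With a continuity correction these become 113 and 146. With a one-sided 0.05 test they are 79 and 109. None is near 55.

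**Step 3. Power at the stated size, 90% versus 75%.** Pooled normal at 55 per arm:

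- null standard error √(2 × 0.825 × 0.175 / 55) = 0.0725
- alternative standard error √(0.2775 / 55) = 0.0710
- power = Φ[(0.15 − 1.96 × 0.0725) / 0.0710] = 54.5%

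The exact figures below come from enumerating both binomial distributions.

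| Method | 55 per arm | 60 per arm (all 120 evaluable) |
|---|---|---|
| Pooled normal | 54.5% | 58.2% |
| Exact, uncorrected chi-square | 55.8% | 58.5% |
| Exact, Fisher | 44.7% | 49.4% |

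**Step 4. Is the effect conservative?** 90 − 75 = 15 points, so the planning effect is the preliminary difference with no discount. For comparison, suppose the true rates are 85% and 75%. This 10-point difference is an illustration, not a protocol figure. The pooled normal power at 55 per arm is then Φ[(0.10 − 1.96 × √(0.32/55)) / √(0.315/55)] = Φ(−0.654) = 25.7% (26.2% by exact chi-square). At 60 per arm it is 27.6% (27.8%).

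**Step 5. Which endpoint do these rates describe?** The 90% and 75% in section 4 are success rates of access sheath placement, which is also the primary outcome named in the Abstract. The primary endpoint in section 6 is narrower: it also requires completing first-stage surgery without major intraoperative complications. The protocol gives no rates for that composite, so every power figure above is for placement alone.

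**The case against.** The strongest defence is that sizing a trial for precision is legitimate, that section 4 openly lists the interval width among its inputs, and that section 3 describes the aim as preliminary. All of this stands. It defends 110 as a precision-based number, but not the statement that 110 is what detecting superiority requires, and section 3 also declares a superiority design.

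Some stronger readings are tempting and not supported:

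- *That the calculation is wrong, or that a stated power is false.* The stated inputs reproduce 55 per arm, and no power is stated.
- *That the trial must be enlarged.* Whether to accept a precision-based trial or to size it for a power target is the sponsor's choice, and the preliminary aim is compatible with the first.
- *That the attrition allowance is a material error.* Section 4 says "Accounting for a potential 10% attrition rate, the adjusted sample size is 120 patients". Strictly, 110 / 0.9 = 122.2, and 120 less 10% leaves 108. That moves power only from 54.5% to 53.7%. The primary endpoint is intraoperative, so losses during the two-week follow-up would hardly touch it.
- *That the Abstract's forward-looking claim, "The findings will provide high-quality evidence to support the integration of EA as an adjunctive therapy in clinical practice", is part of the sample size error.* It is general language about the trial, not a property attached to 110, and changing it would be an editorial matter.
- *That a non-significant result will be taken as evidence against electroacupuncture.* A reader might fear this, but the protocol does not say how such a result would be interpreted.

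**Conclusion.** The point holds as a mismatch between a correctly computed precision-based sample size and the detection property claimed for it. For sheath placement rates of 90% and 75% at two-sided 0.05, 55 per arm gives about 55% power by the normal or chi-square calculation and about 45% with Fisher's exact test. If all 120 patients are evaluable, the figures are about 58% and 49%. Power of 80% would need about 100 per arm. The description of the effect as conservative is contradicted by the section's own rates.

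The conclusion does not depend on the choice of test, since none of those examined reaches 60% at either size. It does rest on the preliminary rates being true, and it applies to placement success. Power for the section 6 composite cannot be calculated from the protocol.

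**What to change.** Keep 120 patients and correct the description in section 4.

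1. Delete the closing clause of the sample size statement, which says the number is needed to detect superiority, and delete the word conservative.
2. Replace them with text such as:

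> n = 110 gives an expected 95% CI width of 0.28 for the difference in UAS placement success if the rates are 90% and 75%. Power to show superiority at two-sided 0.05 is then about 55% (58% if all 120 are evaluable), and for 85% versus 75% about 26% (28% if all 120 are evaluable). These figures are for the chi-square test.

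3. Add that these rates are for placement, that the section 6 primary endpoint also requires completing first-stage surgery without major intraoperative complications, and that no rates for that composite were available for planning.
4. State that the primary result will be presented as an estimate of the difference with its 95% confidence interval, in keeping with the preliminary aim in section 3.

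The cost is protocol wording, with no extra patients, and a less favourable stated figure. The change does not raise the chance of detecting the effect; it makes that chance visible. If the sponsor prefers to keep the detection claim, it should state a power and recompute. For 80% at these rates that means about 200 evaluable patients, or 200 / 0.9 = 222.2, so about 223 to 224 enrolled at 10% attrition.

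### Enrolling 120 leaves 108 evaluable patients after the stated 10% attrition, 2 short of the required 110; 120 covers about 8.3%

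*Protocol*

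**What the plan says.** Section 4 of the Protocol sizes the trial on a preliminary "90% success rate of UAS placement in the EA group" "compared to 75% in the sham EA group". The other inputs are "With a two-sided significance level of 0.05", "a 1:1 allocation ratio between groups" and "0.28 confidence interval width". From these it concludes that "a total of 110 participants (55 in the EA group and 55 in the sham EA group) are required to detect this superiority". The next sentence makes the attrition adjustment: "Accounting for a potential 10% attrition rate, the adjusted sample size is 120 patients". The Abstract and Section 3 (Study design) both repeat the enrolment of 120. Section 4 does not say how the 10% was applied.

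**The concern.** An attrition allowance is there so that the required number is still available after the expected losses. Here the required number, the loss rate and the enrolment stand in two consecutive sentences, and the enrolment does not do this: at the protocol's own loss rate, fewer than 110 patients remain. The 110 also has no slack, because 55 is the smallest whole number per arm that meets the stated interval width. A reader who takes Section 4 at face value would credit the trial with slightly more protection against loss than it has.

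**Working it through.** **Inputs, all from Section 4:** p1 = 0.90 (EA), p2 = 0.75 (sham EA), two-sided level 0.05 (z = 1.96), 1:1 allocation, full interval width W = 0.28, attrition 10%, enrolment 120.

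**Step 1. Reproduce the 110.** For a Wald 95% interval for a difference of two proportions:

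- n per arm = [p1(1 − p1) + p2(1 − p2)] x (2 x 1.96 / W)²
- = (0.09 + 0.1875) x (3.92 / 0.28)² = 0.2775 x 196 = 54.39
- Rounded up: 55 per arm, 110 in total. This matches the protocol. Unrounded, the total is 108.78.

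**Step 2. Apply the stated attrition to the stated enrolment.**

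- 120 x 0.90 = 108, or 54 per arm
- Shortfall against 110: 2 patients
- Attrition that 120 can absorb: 1 − 110/120 = 10/120 = 8.3%

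**Step 3. See how 120 could have arisen.**

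| Route | Result |
|---|---|
| 110 / 0.90 | 122.2, so 123 (124 with equal arms) |
| 110 x 1.10 | 121 (122 with equal arms) |
| 108.78 / 0.90 | 120.9, so 121 |
| 108.78 x 1.10 | 119.65, so 120 |

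The last route gives exactly 120, and per arm it gives 54.39 x 1.10 = 59.83, so 60. The protocol does not say that it was used. Adding 10% of the smaller number is not the same as allowing for a loss of 10% of the larger one: 120 x 0.90 = 108 is below even the unrounded 108.78, though by less than one patient.

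**Step 4. Size the effect at 90% versus 75%.**

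Width = 2 x 1.96 x √(0.2775 / n):

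- n = 55 per arm: 0.2784
- n = 54 per arm: 0.2810

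Power of the two-sided 0.05 normal-approximation test with pooled variance under the null:

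- n = 55 per arm: 54.5%
- n = 54 per arm: 53.7%
- Difference: 0.8 percentage points

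**The case against.** There is a good case that this hardly matters.

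- **The figure 120 has a plausible origin.** It follows from a common add-on convention with rounding left to the end (last row of the table). A reader might infer that 110, 10% and 120 are arithmetically irreconcilable, or that 120 has no derivation. The document does not support that: if 110 is the rounded requirement and the 10% is an add-on to the unrounded one, the three figures fit together. What remains is that the add-on does not deliver the protection the sentence describes.
- **The precision target is given to two decimals.** A width of 0.2810 still reads as 0.28. A reader might infer that the trial fails its precision target. That shows only at a third decimal that the protocol does not state.
- **The sized endpoint is unlikely to lose many patients.** Section 6 defines it by sheath placement and completion of the first-stage procedure, Section 5.1 places the intervention in the same session, and the Abstract plans an intention-to-treat analysis. Losses during the two weeks after surgery would affect stone clearance and adverse events, on which the trial was not sized. This stands as a reason to expect little practical harm. It is an inference, since the protocol gives no loss rate for each endpoint and itself chose 10% when sizing the trial.

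None of this makes 108 equal to 110. It does limit the point to the wording of the allowance.

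**Conclusion.** The point holds as a minor error in a stated figure. At the protocol's own 10% attrition, 120 enrolled leaves 108 evaluable patients, 2 fewer than the number Section 4 calls required; the allowance actually built in is about 8.3%. The cost is a change in interval width from 0.278 to 0.281 and a power loss of less than 1 percentage point. These figures rest on the stated 90% and 75%, equal losses in the two arms, and a Wald interval. The interval method is not named in the protocol, but it reproduces the 110 exactly.

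A reader might go further and infer that the trial must enrol 123 or 124. The size of the effect does not call for that, and actual loss to an intraoperative endpoint is probably below 10%. Whether a sample set by interval width is large enough to show superiority is a separate question that this point does not settle.

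**What to change.** Keep enrolment at 120 and correct the one sentence in Section 4, in either of two ways:

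- state that 120 allows for about 8% attrition (10 of 120) while keeping 110 evaluable; or
- keep the 10% and state that 108 evaluable patients (54 per arm) are then expected, with a 95% confidence interval width of about 0.281 at 90% versus 75%.

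The cost is one sentence and a slightly less favourable stated allowance or precision. No patients are added, and the 120 in the Abstract and Section 3 stays as it is.
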